### Power calculations and rationale

The hypotheses of the ECHO study are that:

**Table Taba:** 

Women who vape during pregnancy will be more likely have a preterm birth and that their infants will have a lower birth weight (LBW), lower neuro-behavioural scores and increased respiratory symptoms when compared with non-smokers.
Women who vape during pregnancy will be less likely to have a preterm birth and their infants will have a higher birth weight, higher neuro-behavioural scores, and fewer respiratory symptoms than when compared with tobacco smokers.

The best available data suggest a prevalence of smoking rate during pregnancy in Ireland is between 9 and 10% [44], whilst the current expected rate of vaping during pregnancy is approximately 5% [45]. The cumulative live birth rates in the three maternity hospitals in Dublin in 2023 were: The Coombe Hospital—6974, The Rotunda Hospital—8442, and the National Maternity Hospital—6880, which will give a projected denominator of approximately 22,000 total live births. The incidence of vaping during pregnancy in the Coombe is 5% [34, 46]; projected to the other three hospitals gives approximately 750–1250 vapers per annum. The calculations in Table 3 give the magnitude of a detectable association with (2-year) prevalence of each condition (odds ratios) or mean differences that are detectable at a power of 80%, with a type I error rate of 0.05. These assume use of simple uncorrected Chi-square test or *t* tests. Detectable effect sizes are presented assuming a range of sample sizes to illustrate how power is maintained under a range of recruitment scenarios. We plan to collect three equally sized groups—non-smokers, smokers, and vapers

**Table 3 Tab3:** Sample size calculation

Sample size (per group)	Baseline incidence		
	10% (wheeze)	6.2% (preterm birth)	5% (low birth weight)
	Detectable odds ratios:		
100	3.00	3.62	3.19
200	2.25	2.63	2.26
300	1.96	2.24	1.91
**400**	**1.80**	**2.04**	**1.74**

Whilst robust data on the effect of vaping during pregnancy on women and infants are lacking, the effects of smoking are well characterised on neonatal anthropometric measurements. Asthma or wheeze has an incidence of approximately 10% within the first 3 years of life [47]. LBW occurs at a frequency of about 5% [48]. PTB occurs in approximately 6.2% of births in Ireland [49]. Maternal smoking has been shown to increase risk of asthma or wheeze in childhood with an odds ratio of 1.8 (95% CI 1.35–2.53). Smoking has also been shown to increase incidence of LBW with an odds ratio of 1.75 (95% CI 1.42–2.10). The odds ratio for PTB conferred by smoking is 1.27 (95% CI 1.20–1.33).

Data on neurocognitive outcomes is lacking; neurocognitive outcomes between groups can be expressed as standardised mean differences (SMD). Table 4 gives indicative detectable differences for each sample size. For reference, caregiver depression has been as a risk factor on the NBAS with a SMD of 0.28 [50] and smoking demonstrated an association of the order of SMD = 0.2–0.4 for executive function including inhibition and self-control [51].

**Table 4 Tab4:** Indicative detectable differences per sample size

Sample size (per group)	Standardised mean difference
100	0.40
200	0.28
300	0.23
**400**	**0.20**

Therefore, we propose to recruit 1200 participants (400 smokers, 400 vapers and 400 non-smoker, non-vaper controls) to generate adequate power and precision to answer our research questions.

In the case that key measurements are missing at rates in excess of 5%, multiple imputation procedures will be considered. We anticipate the likelihood of missing data is small given the standard procedures in place to manage the study centrally.

Case report form (CRF) data entry into REDCap will include extensive data validation checks. Missing data will be monitored, and strategies will be developed to minimise its occurrence. Central statistical data monitoring will summarise missing or inconsistent data periodically. The study workbook will be approved by the chief investigator and validations will also be made that will cross-check the study workbook with the ECHO study electronic CRF.

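### The 400 per group is benchmarked on smoking-versus-non-smoking odds ratios, but both hypotheses concern vapers, whose contrasts must be smaller if both hypotheses are true

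*Protocol article*

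**What the plan says.** The protocol article, under Power calculations and rationale, sets out two hypotheses. The first compares vapers with non-smokers: "Women who vape during pregnancy will be more likely have a preterm birth and that their infants will have a lower birth weight", with "lower neuro-behavioural scores and increased respiratory symptoms when compared with non-smokers". The second compares vapers with smokers: "Women who vape during pregnancy will be less likely to have a preterm birth and their infants will have a higher birth weight", with "fewer respiratory symptoms than when compared with tobacco smokers".

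Table 3 lists odds ratios "detectable at a power of 80%, with a type I error rate of 0.05". On the test, the text says: "These assume use of simple uncorrected Chi-square test" (or t tests for means). The highlighted row, 400 per group, gives 1.80 for wheeze (10% baseline), 2.04 for preterm birth (6.2%) and 1.74 for low birth weight (5%).

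The text after Table 3 acknowledges that robust data on vaping are lacking and cites smoking effects instead. For wheeze: "Maternal smoking has been shown to increase risk of asthma or wheeze in childhood with an odds ratio of 1.8" (95% CI 1.35–2.53). For low birth weight the odds ratio is 1.75, and for preterm birth 1.27. After Table 4 it concludes that 1200 participants, 400 in each of three groups, will be recruited "to generate adequate power and precision to answer our research questions". It gives no expected effect for vapers against controls or against smokers.

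**The concern.** The cited benchmarks describe smokers against non-smokers, which neither hypothesis tests. For wheeze, and nominally for low birth weight, the highlighted row of Table 3 coincides with those benchmarks, and this coincidence is the visible basis for 400 per group.

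The two hypotheses together place vapers between controls and smokers. Each vaper contrast is then only part of the smoking effect, so a sample that just detects the whole will not detect both parts with similar power.

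What is at stake is interpretation. A non-significant vaper-versus-control result, from a study described as adequately powered, could be read as reassurance about vaping. The Dissemination section expects the findings to inform national and international guidelines.

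**Working it through.** **Inputs from the protocol.** 400 per group; control wheeze risk 10%; smoking odds ratio (OR) 1.8 (95% CI 1.35–2.53); type I error 0.05; uncorrected chi-square test. Sidedness is not stated. A one-sided test would give a detectable wheeze OR of 1.70, so Table 3 is two-sided.

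**Assumption not in the protocol.** Where vapers lie between controls and smokers. The log-odds midpoint is used first, then other positions.

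**Formula.** With d the risk difference, s0 = √[2p̄(1−p̄)/n] and s1 = √{[p1(1−p1)+p2(1−p2)]/n}, power is Φ[(d − 1.96·s0)/s1] plus a small opposite-tail term.

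**Step 1: reproduce Table 3.** Solving for 80% power at a 10% baseline gives 2.99, 2.25, 1.96 and 1.81 for 100 to 400 per group. Table 3 prints 3.00, 2.25, 1.96 and 1.80, so the wheeze column reproduces.

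**Step 2: smokers versus controls.** Smoker odds are (0.10/0.90) × 1.8 = 0.20, so the risk is 0.20/1.20 = 16.7%. Then d = 0.0667, s0 = 0.0240, s1 = 0.0239, and power is Φ(0.82) = 79%.

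**Step 3: the constraint.** OR(vaper v control) × OR(smoker v vaper) = OR(smoker v control) = 1.8. If one factor is 1.8, the other is 1.0 and one hypothesis is false.

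**Step 4: vapers at the midpoint.** Each OR is √1.8 = 1.342. Vaper odds are 0.1111 × 1.342 = 0.149, so the risk is 13.0%.
- Vapers v controls: d = 0.0297, s0 and s1 = 0.0225; Φ(−0.64) gives 26%.
- Smokers v vapers: d = 0.0369, s0 and s1 = 0.0251; Φ(−0.49) gives 31%.

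Simulation with 200,000 runs gives 25.9% and 31.2%. A midpoint on the risk scale (13.3%) gives 31% and 26%. Reaching 80% at the log-odds midpoint would need about 1,805 and 1,452 per group respectively.

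**Step 5: other positions and the cited interval (wheeze).**

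| Smoking OR | Position of vapers (share of log OR) | Power v controls | Power v smokers |
|---|---|---|---|
| 1.8 | one quarter | 10% | 57% |
| 1.8 | midpoint | 26% | 31% |
| 1.8 | three quarters | 53% | 12% |
| 1.35 | midpoint | 10% | 11% |
| 2.53 | midpoint | 57% | 71% |

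At OR 1.8 the weaker contrast is at most about 28% at any intermediate position. For 80% on both contrasts the smoking OR would have to be about 1.81 × 1.64 = 2.96, above the cited upper limit of 2.53.

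**Step 6: the other outcomes.**
- Preterm birth: the detectable OR is 2.04 and the cited smoking OR is 1.27. Smokers v controls has only about 14% power; the midpoint vaper contrasts have about 7% each.
- Low birth weight: at the 5% baseline the detectable OR at 400 per group is 2.17, not 1.74. Smokers v controls at OR 1.75 has 49% power; the midpoint contrasts have 15% and 18%. Much of that shortfall comes from the separate column error.
- Continuous scores: the cited smoking standardised mean difference (SMD) for executive function is 0.2–0.4. Half of this, 0.1 to 0.2, gives 29% to 81% power per contrast by t test at 400 per group.

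**The case against.** The strongest defence is that Table 3 is a table of detectable effects, not a claim about the true vaping effect. Any two groups with a 10% reference risk and an OR of 1.80 have about 80% power, vapers and controls included. This stands: the wheeze column is right, and nowhere does the protocol claim 80% power at an OR of 1.34. What it does not cover is the later step from smoking odds ratios to a statement of adequacy for research questions about vaping.

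It also stands that the hypotheses fix an order and not a midpoint, and that the vaping effect is unknown. The 26% and 31% are therefore conditional figures and need the range beside them. The ceiling of about 28% on the weaker contrast does not depend on the midpoint, but it does depend on a smoking OR of 1.8.

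Two stronger readings are tempting. A reader might infer that the study has almost no chance of showing vaping to be worse than no exposure and better than smoking. The protocol's own ranges do not support that: at the upper limit for wheeze the midpoint contrasts reach 57% and 71%, and at half of SMD 0.4 each contrast reaches 81%. A reader might also judge the design by the chance that both contrasts are significant together. The protocol states two separate hypotheses and no rule requiring both. The Objectives ask whether risk is higher or lower, and the planned analyses speak of estimating group differences, so joint significance is not its standard.

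**Conclusion.** The adequacy statement is wrong as written for the binary primary outcomes. The fault is the inference from smoking effects to vaping questions; the wheeze arithmetic is sound. At the cited wheeze OR of 1.8, the familiar 80% belongs to smokers versus controls, and at least one of the two hypothesised vaper contrasts has no more than about 28% power wherever vapers lie between the other groups.

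This rests on both hypotheses being true, two-sided testing at 0.05, and 400 analysed per group with no losses. One-sided testing would raise the midpoint figures only to 37% and 43%. The coincidence between benchmark and detectable effect is clean for wheeze, only nominal for low birth weight, and absent for preterm birth. The continuous scores are much less affected if the smoking effect is near the top of its cited range.

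**What to change.** Under Power calculations and rationale:
1. State that, for wheeze, 80% power at an OR of 1.80 corresponds to the cited smoker-versus-control effect.
2. Add to Table 3, or beside it, the power for vapers v controls and vapers v smokers at stated intermediate effects. Name the assumed position, and give the range over other positions and over the cited confidence interval.
3. Replace the claim that recruitment will suffice "to generate adequate power and precision to answer our research questions" with the effect each vaping contrast can detect or exclude at 400 per group. For wheeze this is an OR of about 1.8 in either contrast: 1.81 upward from controls at 10%, and 1.81 downward from smokers at 16.7%.
4. State that a non-significant vaper contrast will be reported with its confidence interval and not read as no difference.

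The low birth weight column should be corrected separately. The cost is protocol wording and two extra columns, with no additional participants and no change of design. The downside is that the stated power becomes less favourable.

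### Table 3's low-birth-weight column is wrong: at 5% baseline and 400 per group the detectable odds ratio is 2.17, not 1.74, and power at the cited smoking odds ratio of 1.75 is about 49%

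*Protocol article*

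**What the plan says.** In its section Power calculations and rationale, the protocol article says Table 3 shows effects ("odds ratios) or mean differences that are detectable at a power of 80%, with a type I error rate of 0.05"). On the method it says "These assume use of simple uncorrected Chi-square test or" t tests, and on allocation "We plan to collect three equally sized groups". The low-birth-weight column is headed "5% (low birth weight") and contains 3.19, 2.26, 1.91 and, in bold, 1.74 for 100, 200, 300 and 400 per group.

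The text after the table repeats the 5% frequency of low birth weight and gives a benchmark: "Smoking has also been shown to increase incidence of LBW with an odds ratio of 1.75" (95% CI 1.42–2.10). It then concludes that 1200 participants, "400 smokers, 400 vapers and 400 non-smoker, non-vaper controls", will give adequate power and precision. Table 2 lists low birth weight as a primary outcome, and the text introducing that table says the primary outcomes informed the sample size calculation.

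**The concern.** The column looks wrong before any calculation. Sample size, power and type I error are the same across each row. At incidences this low, a rarer outcome yields fewer events and so needs a larger odds ratio to be detected. The 5% column should therefore lie above the other two. Instead it lies below the 6.2% preterm-birth column in every row (3.19 against 3.62, 2.26 against 2.63, 1.91 against 2.24, 1.74 against 2.04). At 300 and 400 per group it also lies below the 10% wheeze column (1.91 against 1.96, 1.74 against 1.80).

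The error flatters the design. The bold 1.74 sits just under the cited smoking odds ratio of 1.75, so a reader will conclude that 400 per group detects a smoking-sized effect on low birth weight with 80% power. If it does not, a null result for this primary outcome carries much less information than the plan implies. The authors expect their findings to inform guidelines, so that matters.

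**Working it through.** **Inputs, all from the section Power calculations and rationale and Tables 3 and 4**

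- Power 80%; type I error 0.05. Sidedness is not stated and is taken as two-sided, because that choice reproduces the other columns and Table 4.
- Uncorrected chi-square test; equal groups of n = 100, 200, 300 or 400.
- Baseline p₁: 10% (wheeze), 6.2% (preterm birth), 5% (low birth weight).

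**Formulas**

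Incidence in the other group at odds ratio OR: p₂ = OR·p₁ / (1 − p₁ + OR·p₁).

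Power = Φ{ [ |p₂ − p₁| − 1.96·√(2p̄(1 − p̄)/n) ] / √([p₁(1 − p₁) + p₂(1 − p₂)]/n) }, with p̄ = (p₁ + p₂)/2. The detectable odds ratio is the one at which this equals 0.80.

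**Step 1. Reproduce the table**

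| Column | | n = 100 | 200 | 300 | 400 |
|---|---|---|---|---|---|
| Wheeze, 10% | printed | 3.00 | 2.25 | 1.96 | 1.80 |
| | recomputed | 2.99 | 2.25 | 1.96 | 1.81 |
| Preterm birth, 6.2% | printed | 3.62 | 2.63 | 2.24 | 2.04 |
| | recomputed | 3.63 | 2.62 | 2.24 | 2.04 |
| Low birth weight, 5% | printed | 3.19 | 2.26 | 1.91 | 1.74 |
| | recomputed | 4.01 | 2.84 | 2.40 | 2.17 |

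Table 4 also reproduces: (1.96 + 0.84)·√(2/n) gives 0.40, 0.28, 0.23 and 0.20. The method is therefore identified, and only the low-birth-weight column fails.

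**Step 2. Power at the cited smoking odds ratio, n = 400**

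- p₂ = 1.75 × 0.05 / (0.95 + 0.0875) = 0.0843; difference 0.0343; p̄ = 0.0672.
- Standard error under the null: √(2 × 0.0672 × 0.9328 / 400) = 0.01770, and 1.96 × 0.01770 = 0.0347.
- Standard error under the alternative: √((0.0475 + 0.0772)/400) = 0.01766.
- z = (0.0343 − 0.0347)/0.01766 ≈ −0.02, so power is 49.2%. Exact enumeration of the chi-square test gives 49.5%.

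The expected difference is almost exactly the critical difference, which is why power is close to one half.

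**Step 3. Check the value 2.17**

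At OR 2.17, p₂ = 0.1025, the difference is 0.0525, p̄ = 0.0763, and the two standard errors are 0.01877 and 0.01867. Then z = (0.0525 − 0.0368)/0.01867 = 0.84, which is 80% power.

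**Step 4. Power at the printed odds ratios**

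At 3.19, 2.26, 1.91 and 1.74 the power is 61%, 56%, 51% and 48% for n = 100, 200, 300 and 400.

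**Step 5. Sample size needed**

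For 80% power at OR 1.75 the formula gives 833.03, hence 834 per group. At OR 1.74 it is 853 per group.

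**Step 6. Can another convention give 1.74?**

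At 5% baseline and n = 400:

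| Variant | Result |
|---|---|
| One-sided test | 2.01 |
| Unpooled variance | 2.16 |
| Arcsine | 2.15 |
| Wald test on the log odds ratio | 2.20 |
| Continuity correction | 2.24 |
| Comparator group twice as large | 2.00 |
| Same, one-sided | 1.86 |
| Entry read as a risk ratio | 2.05 |

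None does. A different baseline does not help either: the four printed values would need baselines of 8.4%, 9.8%, 11.2% and 12.0%, so no single baseline fits the column.

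**A possible cause (conjecture only).** The correct alternatives from a 5% baseline are p₂ = 17.43%, 12.99%, 11.23% and 10.25%. Dividing their odds by the preterm-birth odds (0.062/0.938) instead of the 5% odds (0.05/0.95) gives 3.19, 2.26, 1.91 and 1.73, very near the printed column. The finding does not depend on this.

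**The case against.** The strongest reply accepts the arithmetic and disputes its weight. Most of its individual points are fair.

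- **The 1.75 is not a declared design assumption.** The protocol cites it as the effect of smoking and says robust data on vaping are lacking. This stands. It is, however, the only effect size given for low birth weight, and the column is wrong whatever benchmark is used.
- **The choice of 400 does not rest on low birth weight alone.** The wheeze benchmark (detectable 1.80, cited 1.8) and the standardised mean difference (detectable 0.20, cited 0.2–0.4) also match at 400 and survive the correction. For preterm birth the protocol openly shows a mismatch (detectable 2.04, cited 1.27) and keeps 400. This too stands: low birth weight is one support among several. But after correction neither obstetric primary outcome has 80% power at its cited smoking effect, and the printed table hides this for one of them.
- **Two-sidedness is inferred, and the hypotheses are directional.** This is true. A one-sided test gives a detectable odds ratio of 2.01 and 61.6% power at 1.75, and it would break the two columns that now reproduce.
- **Table 3 is only indicative.** The planned analyses are mixed or generalised additive models with confounders, and birth weight in grams and birth centile are also collected. These limit what is lost for the science. They do not make the printed figures correct for the test they are said to describe.

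**Conclusion.** The low-birth-weight column is wrong as written in all four rows, in the favourable direction. At 400 per group the odds ratio detectable with 80% power is 2.17, not 1.74. Power at the cited smoking odds ratio of 1.75 is 49.2%, and even at the upper limit of its confidence interval, 2.10, it is 76%.

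This rests on the protocol's own inputs (5% baseline, uncorrected chi-square test, equal groups, type I error 0.05) and on one inference, two-sided testing, which the rest of the tables supports. It assumes complete data and no covariate adjustment, as Table 3 does. Because low birth weight is a primary outcome said to have informed the sample size, the correction is required. It does not show that 400 per group is unsuitable for wheeze or for the standardised mean differences, whose figures reproduce.

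**What to change.** 1. Replace the low-birth-weight column of Table 3 with 4.01, 2.84, 2.40 and 2.17 for 100, 200, 300 and 400 per group.
2. Where the smoking odds ratio of 1.75 is cited, add that 400 per group gives about 49% power (two-sided 0.05) for low birth weight at that value, and 80% power only from an odds ratio of about 2.17.
3. Qualify the concluding statement on adequate power, so that it no longer implies 80% power for a smoking-sized effect on low birth weight.
4. State that the type I error is two-sided.

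The cost is one table column and a few words of text. Recruitment, outcomes and analysis do not change. The stated position on low birth weight becomes less favourable, and a null result for it would then be read with the right caution.

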### Sample size and planned statistical analyses

We will aim to achieve as representative as sample as possible of each population. Descriptive statistics on outcomes and other risk factors will be derived for the three groups at each timepoint. An assessment of representativeness of each group will be made based on baseline indicators. In the case that key measurements are missing at rates in excess of 5%, multiple imputation procedures will be considered. Longitudinal analyses of the outcomes will be conducted using (normal or logistic) multilevel (mixed effects) models to account for repeated measurements within individuals. Generalised additive models (GAMs) or logistic GAMs (lGAM) will be used to estimate group differences in each outcome over time in a fully flexible model that can allow for non-linear change without overfitting. Potential confounders or modifiers of the outcomes will be incorporated into the models as predictors or by utilising interaction terms as appropriate.

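### Tables 3 and 4 give detectable effects for unadjusted two-group tests, and the conclusion that 400 per group suffices makes no allowance for the planned confounder adjustment

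*Protocol article*

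**What the plan says.** Under *Power calculations and rationale*, Table 3 gives detectable odds ratios and Table 4 gives standardised mean differences (SMDs), for 100 to 400 women per group. The effects are described as "detectable at a power of 80%, with a type I error rate of 0.05". The simplification is disclosed: "These assume use of simple uncorrected Chi-square test" or t tests. At 400 per group the printed values are OR 1.80 (wheeze, 10% baseline), OR 2.04 (preterm birth, 6.2%), OR 1.74 (low birth weight, 5%) and SMD 0.20. Table 4 is called indicative.

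Under *Sample size and planned statistical analyses* the analysis is different: normal or logistic multilevel models and generalised additive models. On covariates it says: "Potential confounders or modifiers of the outcomes will be incorporated into the models as predictors or by utilising interaction terms as appropriate". Under *Population* the groups are defined by self-reported exposure checked against breath carbon monoxide, so they are not randomised.

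The section then concludes "we propose to recruit 1200 participants (400 smokers, 400 vapers and 400 non-smoker, non-vaper controls") in order "to generate adequate power and precision to answer our research questions".

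**The concern.** The power figures belong to a crude comparison, whereas the research questions will be answered by an adjusted one. Where exposure is self-selected, the covariates worth adjusting for are associated with exposure. That association inflates the variance of the adjusted group coefficient by about 1/(1−R²), where R² is the share of variance in the exposure contrast that the covariates explain. A crude formula sets R² to zero, which is reasonable in expectation under randomisation but not in this cohort.

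The disclosure is not carried into the conclusion about adequacy. A reader could take 1.80, 2.04 and 0.20 as effects that the adjusted analysis detects with 80% power, and could then read too much into a null adjusted comparison of vapers with controls. The protocol expects its findings to inform national and international guidelines.

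**Working it through.** **Inputs from the protocol.** Power 80% and type I error 0.05 (two-sided reproduces the figures, one-sided does not); equal groups of 400; baselines 10%, 6.2% and 5%; printed effects as above.

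**Step 1: reproduce the printed figures.** With p₂ = p₁·OR/(1 − p₁ + p₁·OR) and p̄ the mean of p₁ and p₂, power for the uncorrected two-proportion test is

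Φ{ [ |p₂ − p₁| − 1.96·√(2p̄(1−p̄)/n) ] / √[ (p₁(1−p₁) + p₂(1−p₂))/n ] }.

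- Wheeze, OR 1.80: p₂ = 0.18/1.08 = 0.1667. Power = Φ[(0.0667 − 1.96 × 0.02404)/0.02392] = Φ(0.82) = 79.3%. The OR detectable at 80% is 1.81, and OR 1.80 needs 407 per group.
- Preterm birth, OR 2.04: p₂ = 0.1188. Power = Φ[(0.0568 − 1.96 × 0.02028)/0.02018] = Φ(0.85) = 80.1%. Detectable OR 2.04; 399 per group needed.
- SMD: (1.960 + 0.842) × √(2/400) = 0.198. Power at 0.20 is 80.7%; 393 per group needed.
- Low birth weight, OR 1.74: p₂ = 0.0839. Power = Φ[(0.0339 − 1.96 × 0.01767)/0.01763] = Φ(−0.04) = 48%. The detectable OR is 2.17, and OR 1.74 needs about 853 per group.

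The wheeze and preterm columns and all of Table 4 reproduce at every sample size, to rounding. The low-birth-weight column reproduces at none: the crude values are 4.01, 2.84, 2.40 and 2.17, against the printed 3.19, 2.26, 1.91 and 1.74. The table shows the problem itself, since the lowest baseline should have the largest detectable odds ratio of the three, and at 400 per group it has the smallest.

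**Step 2: allow for adjustment.** Replace 400 by 400 × (1 − R²). R² is an assumption, because the protocol gives none.

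| R² | Effective n per group | Power: wheeze OR 1.80 | Power: preterm OR 2.04 | Detectable OR: wheeze | Detectable OR: preterm | Detectable OR: low birth weight |
|---|---|---|---|---|---|---|
| 0 | 400 | 79% | 80% | 1.81 | 2.04 | 2.17 |
| 0.05 | 380 | 77% | 78% | 1.83 | 2.07 | 2.21 |
| 0.10 | 360 | 75% | 76% | 1.86 | 2.11 | 2.25 |
| 0.20 | 320 | 70% | 71% | 1.93 | 2.19 | 2.35 |
| 0.30 | 280 | 64% | 65% | 2.01 | 2.30 | 2.47 |

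To give R² a scale, take one normal covariate shifted by d standard deviations between two equal groups: R² = d²/(d²+4) and AUC = Φ(d/√2). Then d = 0.74 gives R² 0.12 and AUC 0.70, and d = 1.19 gives R² 0.26 and AUC 0.80.

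**Step 3: check by simulation.** Adjusted logistic regression for wheeze used 400 per group, 10% control incidence, conditional OR 1.8, and one covariate shifted upwards in the exposed group. At R² from 0.12 to 0.26, power was about 66-75% if the covariate does not affect outcome. It was about 69-78% if the covariate also raises risk (log OR 0.2-0.4 per SD), because more events then occur.

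**Step 4: continuous outcomes.** The detectable SMD is 0.198 × √[(1 − R²_outcome)/(1 − R²)], where R²_outcome is the share of outcome variance that the covariates explain. If that share is zero, the SMD is 0.21, 0.22 and 0.24 at R² 0.10, 0.20 and 0.30. If the two shares are equal, the SMD stays at 0.198.

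**The case against.** The strongest reply is that nothing is hidden. The protocol states the simple-test assumption openly, calls Table 4 indicative and prints rows for smaller groups. The row for 300 per group (OR 1.96, OR 2.24, SMD 0.23) is numerically the R² = 0.25 case, since 400 × 0.75 = 300. This stands in part: the point is a missing allowance, not concealment or an arithmetic slip. However, the smaller rows are offered as recruitment scenarios, and the conclusion rests on the 400 row as printed.

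A reader might infer that 400 per group cannot deliver the stated effects. The protocol does not support so flat a statement, because the size of the loss depends on an R² that it does not give. At 0.05 the detectable effects hardly move. A covariate that also predicts outcome makes the loss smaller than the plain n × (1 − R²) figures, and for SMDs it can remove the loss entirely.

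A reader might equally infer that the crude test at least has its stated power for every outcome. It does not for low birth weight.

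It can also be said that a null result would be judged from its confidence interval, which already reflects the adjustment. Further, for preterm birth the protocol's own smoking odds ratio of 1.27 has only about 13.5% crude power at 400 per group, so moving 2.04 to 2.11-2.30 makes little difference at that effect. Both are fair and limit the consequence. Neither justifies carrying crude figures into a statement about the adjusted research questions.

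**Conclusion.** The point holds as a missing allowance. The printed wheeze, preterm and SMD figures are correct for crude tests, but 400 per group leaves almost no slack. For the two binary outcomes, covariates that predict exposure take power at the printed odds ratios below 80%. Under the simple variance-inflation rule the loss is about 2 power points at R² 0.05 and about 15 at 0.30. It is smaller if the confounder also raises risk. For Table 4 the loss is possible but may be fully offset.

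This rests on an assumed R² range, on covariates associated with exposure, and, in the simulation, on a covariate that runs higher in the exposed group. The low-birth-weight column is a separate and larger discrepancy (2.17 against 1.74 before any adjustment), and it must be put right before an allowance is applied to it.

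**What to change.** Keep N = 1200 and change the text and tables only.

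- Correct the low-birth-weight column of Table 3 to 4.01, 2.84, 2.40 and 2.17 at 100, 200, 300 and 400 per group.
- Label the figures in Tables 3 and 4 as crude best-case values.
- Add the detectable effects of the adjusted contrast at 400 per group for assumed R² of 0.1, 0.2 and 0.3: wheeze OR 1.86, 1.93, 2.01; preterm OR 2.11, 2.19, 2.30; low birth weight OR 2.25, 2.35, 2.47; SMD up to 0.21, 0.22, 0.24, with a note that these SMDs apply if covariates explain no outcome variance.
- Tie the adequacy statement to those values.
- Once booking data exist, estimate R² for each pairwise contrast from baseline covariates, without looking at outcomes, and use it in place of the range.

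The cost is a few lines of calculation and a table revision, with no extra participants, visits or measurements. The downside is that the adjusted detectable effects read slightly less favourably than the present ones. The low-birth-weight correction is a larger change, but it is due in any case.
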